# Objective of Observational Study

This observational study aims to verify the weight reduction effects and safety of Envlo Tab. or Envlomet SR Tab. in patients with Type 2 Diabetes over a 24-week period in a real-world clinical setting.

## Primary Objectives

Change in BMI and weight at Weeks 24 compared to baseline

## Secondary Objectives

The study will evaluate the following effects of administration of Envlo Tab. or Envlomet SR Tab.:

1. Change in BMI and weight at 12 weeks compared to baseline
2. Proportion of subjects achieving ≥5% reduction in BMI and weight at 12 and 24 weeks compared to baseline
3. Change in body composition index (body fat mass, visceral fat mass, muscle mass, waist/hip circumference) at 12 and 24 weeks compared to baseline
4. Change in HbA1c at 12 and 24 weeks compared to baseline
5. Change in FPG at 12 and 24 weeks compared to baseline
6. Change in blood pressure (systolic, diastolic) at 12 and 24 weeks compared to baseline
7. Proportion of subjects achieving HbA1c < 7% at 12 and 24 weeks compared to baseline
8. Proportion of subjects achieving HbA1c < 6.5% at 12 and 24 weeks compared to baseline
9. Proportion of subjects achieving therapeutic response [change in HbA1c (baseline HbA1c – HbA1c at each evaluation time point) > 0.5% or HbA1c < 7%] at 12 and 24 weeks compared to baseline

## Exploratory Objectives (Exploratory Evaluation)

The effects of administering Envlo Tab. or Envlomet SR Tab. will be explored as follows:

1. Change in lipid levels (total cholesterol, LDL-C, HDL-C, triglycerides) at 12 and 24 weeks compared to baseline
2. Change in liver function markers (AST, ALT, γ-GTP) at 12 and 24 weeks compared to baseline
3. Change in renal function markers [e-CFR, UACR, UGC (Urine Albumin to Creatinine Ratio), UGCR (Urine Glucose to Creatinine Ratio)] at 12 and 24 weeks compared to baseline
4. Change in other body composition analyzer indices (body water, intracellular water, extracellular water, extracellular water ratio, abdominal fat percentage, etc.) at 12 and 24 weeks compared to baseline

## Safety Assessment

The following safety aspects of Envlo Tab. or Envlomet SR Tab. will be assessed:

1. Incidence rate and number of occurrences of Adverse Drug Reactions (ADRs)
2. Incidence rate and number of occurrences of Serious ADRs (SADRs)
3. Adverse Events of Special Interest^*^

^*^ Hypoglycemia, urinary tract infection, genital infection, frequent urination, polyuria

1. Laboratory tests, vital signs, physical examination results

# Selection of Subjects

## Number of Subjects

At least 240 subjects (minimum number to ensure statistical significance considering about 15% dropouts rate)

## Rationale

This study is a large-scale, prospective, multicenter, non-interventional database observational study aimed at observing the weight loss effects, efficacy, and safety of Envlo Tab./Envlomet SR Tab. in patients with Type 2 diabetes over 24 weeks.

As a single-arm observational study, the number of subjects was calculated using G*Power 3.1.9.7, referencing the mean and standard deviation of the changes in weight and body mass index (BMI) from baseline to 12 or 24 weeks from previous Phase 2 and Phase 3 clinical studies (Figure 2) ^20)^

[Assumptions]

- Effect size: 0.25 (Mean of difference 2.5, SD of difference 10.0)
- Power: 0.95
- α error: 0.05
- Drop-out rate: 30%

[figure not shown]

Figure 2. Sample Size Calculation (G*Power)

Based on previous studies, assuming an average weight change of 2.5 kg and a standard deviation of 10.0 for the intervention with Envlo Tab. or Envlomet SR Tab., the effect size is 0.25. Setting the power: 0.95, α error: 0.05, the total required sample size is estimated to be approximately 210 subjects. Considering a drop-out rate of about 15%, we plan to recruit around 240 subjects.

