Following these therapeutic guidelines, the use of SGLT-2 inhibitors has been increasing recently. SGLT-2 inhibitors increase urinary glucose excretion, leading to a relative decrease in insulin secretion and an increase in the glucagon/insulin ratio. This promotes lipolysis and increases ketone body production. The “Super-fuel” hypothesis suggests that in diabetic patients, ketone bodies in the blood serve as an effective energy source for the myocardium, improving cardiac function^8), 9)^. This metabolic benefit implies that SGLT-2 inhibitors can provide broad benefits beyond diabetes treatment, potentially aiding in managing obesity, hypertension, and dyslipidemia.

In particular, the glucose excreted in the urine due to SGLT-2 inhibitors is estimated to be 60-80 g daily, comparable to an energy expenditure of 230-310 kcal, similar to the energy burned by running for 30 minutes daily^10)^. Therefore, using SGLT-2 inhibitors in patients with diabetes who do not experience weight loss can still offer metabolic benefits related to weight reduction. The initial weight loss with SGLT-2 inhibitors is mainly due to reduced hepatic glycogen and dehydration. However, long-term weight loss involves increased fatty acid oxidation and a reduction in visceral and subcutaneous fat due to increased free fatty acid release from adipocytes^11)^. Existing literature indicates that the use of SGLT-2 inhibitors can result in a weight loss of approximately 2-3 kg within the first six months^11)^.

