## Exclusion Criteria

Individuals who meet any of the following exclusion criteria will be excluded from this observational study:

1) Individuals with diabetes other than Type 2 Diabetes (e.g., Type 1 Diabetes, Diabetic Ketoacidosis, Gestational Diabetes, etc.)

2) Individuals who fall under the contraindications for administration according to the approved conditions of Envlo Tab./Envlomet SR Tab.

- Patients with hypersensitivity or a history of hypersensitivity to any component of Envlo Tab. or Envlomet SR Tab.

- Patients with an eGFR less than 30 mL/min/1.73 m²

- Patients with renal impairment with an eGFR less than 60 mL/min/1.73 m², end-stage renal disease, or those on dialysis

- Individuals with moderate to severe hepatic impairment (AST or ALT > 3 times the upper limit of normal, Total Bilirubin > 2 times the upper limit of normal, hepatitis, or liver failure)

- Individuals classified as class III or IV according to the New York Heart Association (NYHA) classification

3) Individuals who have undergone treatment with obesity medications or weight loss drugs, or other treatments (surgery, diet, etc.) leading to unstable weight within 3 months prior to the enrollment date

4) Individuals with mental incapacity

5) Pregnant or breast-feeding women

6) Individuals participating in another clinical study and receiving (applying) investigational drugs or investigational medical devices

7) Individuals deemed unsuitable for participation in this observational study based on the judgment of the investigator (responsible physician)

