### Safety Analysis Set

Subjects who meet the inclusion/exclusion criteria, have been enrolled in this study, received the investigational product at least once according to the approved indications, and have undergone safety evaluations will be included in the safety analysis set.

1. **Methods of Analysis**
2. **General Principles**

Continuous variables will be presented as descriptive statistics (number of subjects, mean, standard deviation, median, minimum, maximum), and categorical variables will be presented as frequencies and percentages. Unless otherwise specified, all tests will be two-sided with a significance level of 5%. All p-values will be reported to a maximum of four decimal places. If not exactly divisible, values will be rounded to two decimal places, rounding up at the third decimal place.

1. **Demographic and Baseline Characteristics**

For the demographic data (age, gender, etc.) and baseline characteristics of the study subjects, continuous variables will be presented as mean, standard deviation, median, minimum, and maximum values, while categorical variables will be presented as frequency and percentage.

1. **Efficacy Endpoints**

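### The sample size rests on an SD of 10.0 for the 24-week weight change that is hard to believe beside a 2.5 kg mean loss and has no source value shown, so calling 240 a minimum is unsupported

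*Protocol*

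**What the plan says.** Protocol Section 3.2 (Rationale) describes a single-arm calculation in G*Power and lists "Effect size: 0.25 (Mean of difference 2.5, SD of difference 10.0"), power 0.95, alpha 0.05 and a dropout rate of 30%. The text below the list repeats the inputs, "assuming an average weight change of 2.5 kg and a standard deviation of 10.0", and concludes: "Setting the power: 0.95, α error: 0.05, the total required sample size is estimated to be approximately 210 subjects". It then applies a dropout of about 15%, not the listed 30%, to reach around 240.

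The section attributes the mean and SD to changes in weight and BMI at 12 or 24 weeks in earlier Phase 2 and Phase 3 studies, citing a Phase 3 study report. It does not say which study, variable or time point supplied 10.0, and it does not show the observed value.

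Section 3.1 calls 240 the "minimum number to ensure statistical significance considering about 15% dropouts rate". Section 8.2 plans a paired t-test or Wilcoxon signed rank test of the change to week 24, two-sided at 5%.

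**The concern.** A paired test depends on the SD of each patient's own change, not on how much patients differ from one another in weight. An SD of 10 kg over 24 weeks is very wide for a mean loss of 2.5 kg. Section 1.1 expects a "weight loss of approximately 2-3 kg within the first six months" for this drug class. Section 3.4, criterion 3, excludes patients with recent obesity drugs or other treatment "leading to unstable weight within 3 months prior to the enrollment date", which removes one source of large swings.

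The effect size, the 210, the stated power and the description of 240 as a minimum all follow from this one number. If it is too large, none of them describes the design. A test against zero would then be almost certain to succeed, and a mean loss well below the 2-3 kg cited could reach significance. The real merit of 240 patients, a precise estimate of the mean loss, would not appear in the rationale.

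**Working it through.** **Inputs from the protocol.** Mean change 2.5 kg, SD of change 10.0 (taken as kg), power 0.95 and dropout 30% (list) or 15% (text), all from Section 3.2; two-sided alpha 0.05 from Sections 3.2 and 8.2; paired t-test from Section 8.2.

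**1. Reproducing the 210.** d = 2.5/10 = 0.25. The normal approximation is (1.960 + 1.645)²/0.25² = 208. The exact noncentral-t calculation gives n = 210 with power 0.9501, which matches the protocol. A one-sided test would need 175.

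**2. What the SD implies.** Take the change as normal with mean -2.5 and SD 10:
- 95% range: -2.5 ± 19.6, that is, from a 22.1 kg loss to a 17.1 kg gain.
- Any gain: P(Z > 0.25) = 0.401.
- Gain of 10 kg or more: P(Z > 1.25) = 0.106.
- Loss of 10 kg or more: P(Z < -0.75) = 0.227.

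**3. Sensitivity to the SD.** The protocol gives no other SD of change, so the SDs below 10 are assumptions. The mean change stays at 2.5 kg. With 15% dropout, 240 × 0.85 = 204 patients are evaluable. Half-width = t(0.975, 203) × SD/√204 = 1.972 × SD/14.28.

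| SD of change (kg) | n for 95% power | Recruited at 15% dropout, n/0.85 | Power with 204 | 95% CI half-width with 204 (kg) |
|---|---|---|---|---|
| 3 | 21 | 25 | >99.99% | 0.41 |
| 4 | 36 | 43 | >99.99% | 0.55 |
| 5 | 54 | 64 | >99.99% | 0.69 |
| 6 | 77 | 91 | >99.99% | 0.83 |
| 7 | 104 | 123 | 99.91% | 0.97 |
| 8 | 136 | 160 | 99.3% | 1.10 |
| 10 | 210 | 248 | 94.5% | 1.38 |

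The half-width is also the smallest observed mean loss that would reach p < 0.05 if the observed SD equals the value in that row.

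**4. Is 240 a minimum at the protocol's own SD?**
- 15% dropout: 210/0.85 = 247.1, so 248 are needed. Recruiting 240 leaves 204, with power 94.5%.
- 30% dropout: 210/0.70 = 300 are needed. Recruiting 240 leaves 240 × 0.70 = 168, with power 89.6%.
- 240 leaves 210 evaluable only if dropout is 1 - 210/240 = 12.5%.
- 210 × 1.15 = 241.5 lies close to 240, so the inflation may have been done by multiplication; the protocol does not say.

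**The case against.** The case for the protocol has real strength. The calculation is correct for its inputs. The protocol says that the SD describes changes in earlier trials, and neither the cited report nor the figure of the G*Power output can be inspected here. A class mean of 2-3 kg says nothing about spread, and criterion 3 excludes only recent treatment-related instability, not unstable weight in general. Some allowance above trial spread is reasonable: ages 19 to 80, BMI from 23 to above 35, three treatment settings, no mandatory visits, and data collected whether or not the drug is taken. Above all, too large an SD makes the study larger than needed, not smaller.

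All of this stands, and it rules out several stronger readings that a reader might infer:
- That 210 is a miscalculation. It is not; only the input is in question.
- That the protocol's own figures prove 10 kg wrong. They do not, because no observed SD of change is reported.
- That 10.0 is really the spread of weight between patients. This is conjecture, and it contradicts what Section 3.2 says about the source. Tests of it through a baseline-to-week-24 correlation need a between-patient SD that the protocol does not give.
- That the study is badly underpowered for weight. At SD 10 and 15% dropout the shortfall is half a percentage point; with a smaller SD there is none.
- That leaving out a confidence interval for the efficacy result is an error. It may be in an analysis plan that is not at hand. Also, the proportion with at least 5% reduction is already a secondary endpoint, which partly guards against over-reading a small mean loss.

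The objection does not make the implied distribution believable or supply the missing source value. It also does not defend the claim that 240 is a minimum.

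**Conclusion.** The concern holds as a challenge to an unsupported input, not to the arithmetic. An SD of 10 kg is hard to reconcile with a 2.5 kg mean loss, and the required n changes tenfold (21 to 210) across SDs of 3 to 10 kg. Any error is conservative: with 204 evaluable patients, power is above 99.9% at SD 7 or less.

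The description of 240 as a minimum is unsupported on either view. With a smaller SD, 240 exceeds what the test needs. With SD 10 it falls short of 248 (15% dropout) or 300 (30% dropout), with power of 94.5% or 89.6%.

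The percentages of large gains and losses assume normality. SDs other than 10 are assumed, not taken from the documents, and the cited report could yet confirm the figure.

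**What to change.** 1. In Section 3.2, check 10.0 against the SD of change from baseline in the cited study report. State the value with its variable and time point, and correct 10.0 if it differs.
2. Restate effect size, n and power over a range of SDs, using one dropout rate reconciled between the assumption list and the text, and inflating by n/(1 - dropout).
3. Keep 240, but justify it by the expected 95% CI half-width for mean weight change: about 0.4 kg at SD 3 to 1.4 kg at SD 10 with 204 evaluable.
4. In Section 3.1, delete the wording that makes 240 a minimum for significance.
5. In Section 8.2, or in the analysis plan if it is not already there, report the mean weight change with its 95% CI beside the paired test, so that it can be read against the 2-3 kg cited in Section 1.1.

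The cost is rewording and one look at a report the sponsor already holds. No patients, visits or procedures change. The rationale may look less favourable if 240 turns out to be well above what the test requires.

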| **Target Number of Subjects** | Approximately 240 subjects (considering about 15% dropouts to ensure statistical significance) |
| **Duration of Observation** | - Expected total study duration: For approximately 24 months from IRB approval   (may be subject to change depending on the subject enrollment rate)   - Observation period per subject: Approximately 24 weeks ( 6 months) |
| **Investigational Drugs** | Envlo Tab. 0.3 mg, Envlomet SR Tab. 0.3/1,000 mg |

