### Primary Efficacy Endpoint

For body mass index (BMI) and weight, descriptive statistics will be presented at baseline and at 24 weeks. The change from baseline to 24 weeks will be analyzed using a Paired t-test or Wilcoxon signed rank test.

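### The sample-size rationale lists a 30% drop-out rate but sizes recruitment on about 15%; at 30%, 240 recruits give about 90% power rather than the stated 95%

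*Protocol*

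**What the plan says.** Section 3.2 (Rationale) sets out its assumptions as a list. The effect is "Effect size: 0.25 (Mean of difference 2.5, SD of difference 10.0"), power is 0.95, the error rate is "α error: 0.05", and the last item reads "Drop-out rate: 30"%. The paragraph below repeats the effect size, power and alpha, arrives at a requirement of roughly 210 subjects, and ends: "Considering a drop-out rate of about 15%, we plan to recruit around 240 subjects".

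The lower rate also appears in the two other places that give the recruitment number:

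- Section 3.1 (Number of Subjects): "At least 240 subjects (minimum number to ensure statistical significance considering about 15% dropouts rate").
- Protocol Synopsis, target number of subjects: "Approximately 240 subjects (considering about 15% dropouts to ensure statistical significance").

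The 30% figure appears once, and no number in the protocol is derived from it.

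**The concern.** One short section gives two drop-out rates, one twice the other, and does not say which is expected. The protocol is version 1.0, so the difference is not left over from a documented amendment, and both figures are in plain text.

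The rate matters in this design. Sections 4.1 and 4.3 say that the study imposes no visits or tests of its own and takes its data from routine care, while the primary endpoint needs a week-24 weight and BMI. How many subjects will lack that value is therefore a real planning question, and the protocol gives two answers. At stake is whether 240 recruits deliver the stated 95% power, and whether 240 can be called a minimum.

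**Working it through.** **Inputs**

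- Effect size 2.5 / 10.0 = 0.25, power 0.95, alpha 0.05: Section 3.2.
- Sidedness: Section 8.2, General Principles, "Unless otherwise specified, all tests will be two-sided with a significance level of 5"%.
- Test: Section 8.2, Primary Efficacy Endpoint, "The change from baseline to 24 weeks will be analyzed using a Paired t-test or Wilcoxon signed rank test". The calculation uses the paired t-test.
- Drop-out: 30% (assumption list, Section 3.2) or about 15% (closing sentence of Section 3.2, Section 3.1, synopsis).
- Assumption made here: every drop-out is lost to the week-24 analysis.

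**Step 1: reproduce the 210.** With n evaluable subjects, the paired t statistic follows a noncentral t distribution with n − 1 degrees of freedom and noncentrality 0.25 × √n. Two-sided power is the probability that its absolute value exceeds the 97.5% point of the central t.

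- n = 209: power 94.92%
- n = 210: noncentrality 0.25 × √210 = 3.62, power 95.01%

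So 210 is the smallest n that reaches 95%, and the protocol's figure reproduces.

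**Step 2: recruitment needed to keep 210**, N = 210 / (1 − d):

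- d = 15%: 210 / 0.85 = 247.06, so 248
- d = 30%: 210 / 0.70 = 300

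**Step 3: what 240 recruits deliver**, n = 240 × (1 − d):

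| Drop-out | Evaluable | Short of 210 by | Power | Type II error |
| --- | --- | --- | --- | --- |
| 12.5% | 210 | 0 | 95.0% | 5.0% |
| 15% | 204 | 6 | 94.5% | 5.5% |
| 30% | 168 | 42 | 89.6% | 10.4% |

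The break-even loss is 1 − 210/240 = 12.5%, a rate stated nowhere in the protocol.

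**Step 4: can any reading of 30% give 240?** Multiplying instead of dividing gives 210 × 1.30 = 273. A one-sided test needs 175 evaluable, and 175 / 0.70 = 250, or 251 if the fraction retained is rounded up conservatively. None of these is 240. The target therefore belongs with the 15% figure, and the 30% is unused.

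**The case against.** The strongest reply is that the operative rate is clear. About 15% stands in every place where the recruitment number is given, while 30% appears once and drives nothing, so it may be a leftover. That is plausible, but the protocol does not say so, and the figure stands in the list headed as the assumptions of the calculation. It still has to be corrected or explained.

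The second reply concerns size, and it stands. At 15% the gap is 6 subjects and about half a point of power, in a passage worded with approximately, about and around. That is a rounding-scale blemish. Even at 30%, power is close to 90% under the protocol's own effect size; 80% would need only 128 evaluable subjects.

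Third, the counts of 204 and 168 treat every drop-out as missing at week 24. The efficacy analysis set in Section 8.2 requires only a post-baseline weight, and the handling of missing week-24 values may be set out in an analysis plan that is not shown. The assumption is the conventional one for sizing, but it remains an assumption.

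Three stronger readings are tempting, and the protocol does not support them:

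- **That the evaluable number is unknown.** It is stated, about 210, and it reproduces. What is unsettled is the expected loss.
- **That 240 came from multiplying by 1.15 instead of dividing by 0.85.** 210 × 1.15 = 241.5 lies close to 240, but no inflation formula is shown, and a rounded 12.5% allowance fits exactly. The cause is a guess, and the shortfall does not depend on it.
- **That the study is underpowered.** It falls short of its own 95% target; on its stated inputs it is not badly powered at either rate.

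**Conclusion.** The point holds as an unreconciled contradiction between a listed 30% drop-out rate and the roughly 15% used to set recruitment. With effect size 0.25, a two-sided 5% paired t-test and all drop-outs lost at week 24, 240 recruits give about 89.6% power at 30%, so the type II error is about twice the stated 5%. At 15% they give about 94.5%, a minor shortfall. The stated 95% is reached only if loss stays at or below 12.5%.

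The description of 240 in Section 3.1 as at least and a minimum is too firm: keeping 210 evaluable needs 248 or 300, and the synopsis says only approximately. A reader might take that phrase as a promise of 95% power, but Section 3.1 speaks of statistical significance and names no power, so this is loose wording rather than a second numerical error.

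This should be fixed before the sample-size justification is relied on. It does not call the feasibility of the primary analysis into question.

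**What to change.** 1. State one expected drop-out rate, with a brief reason for it, and use it in the synopsis, in Section 3.1 and in both places in Section 3.2.
2. Keep 240 and say what it delivers: 204 evaluable and about 94.5% power if the rate is 15%, or 168 evaluable and about 90% power if it is 30%. Say that drop-outs are assumed to contribute no week-24 value.
3. In Section 3.1, replace the wording that makes 240 a floor needed for statistical significance with wording that matches the approximate target in the synopsis.

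The cost is wording in three places and no extra patients. Only if the sponsor wants to keep the 95% claim does enrolment have to change: to 248 at 15% (8 more) or 300 at 30% (60 more).

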## Inclusion Criteria

Select individuals who meet all of the following criteria:

1. 1) Adults aged 19 to 80 years, both male ∙and female
2. 2) Patients with Type 2 Diabetes who, based on medical judgment by the investigator (responsible physician) and according to the approved indications, are about to receive Envlo Tab. or Envlomet SR Tab. for the first time

- Enavogliflozin monotherapy

- Enavogliflozin combination therapy with two agents (in combination with metformin)

- Enavogliflozin combination therapy with three agents (in combination with metformin and a DPP4 inhibitor)

1. 3) Patients with pre-obesity or higher stages according to the 2022 Obesity Treatment Guidelines of the Korean Endocrine Society*

* Obesity Treatment Guidelines of the Korean Endocrine Society

- Pre-obesity: BMI 23-24.9 kg/m^2^

- Stage 1 obesity: BMI 25-29.9 kg/m^2^

- Stage 2 obesity: BMI 30-34.9 kg/m^2^

- Stage 3 obesity: BMI >35 kg/m^2^

4) Individuals who plan to engage in appropriate exercise and dietary therapy for blood glucose control during the observational study period

5) Women of childbearing potential and men who agree to use appropriate contraceptive methods* or have no plans for pregnancy during the observational study period

*Hormonal contraceptives, intrauterine device (IUD) or intrauterine system (IUS) implants, vasectomy, tubal ligation, double barrier methods (simultaneous use of cervical cap or diaphragm with male condom), etc.

6) Individuals who have listened to and understood the detailed explanation of the observational study and the characteristics of the investigational products, and have voluntarily signed a written informed consent agreeing to participate in the study and to comply with subject precautions during the study period

